### Exploratory moderation analyses

The potential moderating effects of race (White vs. Black), sex, income (above. vs. below federal poverty level), past-month illicit drug use, and elevated negative affective symptoms (scoring above threshold on the DASS stress, anxiety, or depression scales) will be explored via path analyses in a manner analogous to multiple regression procedures [60]. The dependent variable in question will be regressed on the main effects for intervention condition, the baseline values of the dependent variable, the baseline moderator variable, and the interaction between the intervention condition and the moderator, where a significant interaction indicates that the effects of the independent variables differ at levels of the moderator. A significant interaction will be followed up with simple slopes analyses at high (i.e., one SD above the mean or clinical cut-off) and low (i.e., one SD below the mean or clinical cut-off) moderator values that will determine the nature of the moderated effect. All continuous variables will be centered prior to the tests for moderation. Variables that directly predict outcome but do not interact with intervention condition will be retained as covariates.

### Mediator analyses

We hypothesize that the predicted advantage for BAI + SFAS and RT + SFAS, relative to control, will be mediated by reductions in alcohol demand, negative affect (DASS total score) and increases in proportionate substance-free reinforcement. Mediators will be tested in separate multilevel (mixed) mediation models using the product of coefficients approach [61]. This approach provides an estimate of the mediated effect by multiplying the regression of the mediator on the independent variable (the “a-path”), and the regression of the outcome on the mediator (the “b-path”), with the independent variable included in the model [62]. The 95% confidence intervals for the mediated effects will be estimated using RMediation [63]. All models will be estimated in Mplus Version 8.4122 with robust maximum likelihood estimation that adjusts standard errors and chi-squares/loglikelihoods to accommodate missing data, non-normal distributions, and nesting by individuals and clinicians. Missing not at random models will also be estimated to determine whether the models are robust to the missing at random assumption of maximum likelihood estimation [52]. Finally, we will conduct exploratory differential (moderated) mediation models that test the hypothesis that alcohol demand (directly targeted by the BAI) will have a larger indirect effect on changes in alcohol use and problems in the BAI + SFAS than in the RT + SFAS condition and that negative affect (targeted by both the RT + SFAS sessions) will have a larger indirect effect on changes in alcohol use and problems in the RT + SFAS condition than in the BAI + SFAS condition.

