## The present study

The primary goal of the proposed study is to establish the efficacy of the BAI + SFAS and BAI + RT approaches, relative to an education only control condition, among high-risk community-dwelling EAs. The primary hypothesis is that at 1, 3, 6, and 12-month follow-ups both BAI + SFAS and RT + SFAS participants will report significantly greater reductions in alcohol use and alcohol problems relative to education control participants, with no differences in outcomes between the two active treatment conditions. A secondary hypothesis is that the predicted advantage for BAI + SFAS and RT + SFAS, relative to education control, will be mediated by changes in alcohol reinforcing efficacy, negative affective symptoms, and proportionate substance-related reinforcement. An additional secondary hypothesis is that the BAI + SFAS and the RT + SFAS conditions will be associated with greater reductions in alcohol demand, proportionate substance-related reinforcement, drug use, and negative affect than the control condition, with no differences in outcomes between the two active treatments.

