#### Drinking and drinking norms

The NIAAA Drinking Assessment will be used to assess past-year alcohol consumption including drinking frequency, typical number of drinks, maximum number of drinks, and frequency of binge drinking. For each item, participants are given a range of frequencies (e.g., every day to 3–11 times in the past year) or a range of drinks (e.g., 1 drink to 25 or more drinks) to choose from. This measure will be administered at baseline and again at 12 months.

Perceived normative drinking will be assessed with the Drinking Norms Rating Form, and the Protective Behavioral Strategies Survey (PBSS) [48] will be used to measure the use of 15 protective behavioral strategies commonly used to reduce alcohol-related harm. Protective behavioral strategies will also be evaluated as a mediator of treatment outcomes.

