## Sample size and power

We have focused our power analysis using Monte Carlo simulations [64] with population estimates and patterns of missingness from our previous trial [24]. These models from our previous trial used generalized mixed models which covaried gender and race/ethnicity, taking into account clustering by individual and therapist. Based on the Monte Carlo estimates comparing BAI + SFAS to control (within *d* = 0.83/0.71, between *d* = 0.33/0.32), we are proposing to recruit 525 subjects (175 per group) for the study. Assuming a similar pattern of attrition as our previous trial will result in *n* = 362 (69%) complete cases, *n* = 95 (18%) cases missing one data point; *n* = 37 (7%) cases missing two data points; *n* = 21 (4%) cases missing three data points; and *n* = 11 (2%) cases missing four data points. We calculated power via Monte Carlo simulations by determining the proportion of 1000 replications for which the null hypothesis that a parameter was equal to zero was rejected for each parameter at alpha = 0.05 (i.e., probability of rejecting the null hypothesis when it is false). This resulted in the following power estimates for typical drinks/problems: treatment effect of BAI + SFAS vs. control = 1.00/1.00; mediation via proportionate substance-free reinforcement = 0.90/0.99; mediation via negative affect = 0.85/0.93; mediation via alcohol demand: 1.00/1.00. While our proposed sample size would not be sufficient to detect very small effects, we believe such small effects are likely to have little clinical meaning in terms of the variables we are assessing in the present trial, and the necessary sample size to detect such effects would be very large (> 1000).

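### Testing each mediator only in its own model cannot show which mechanism carries the treatment effect; a joint multiple-mediator model should be added beside the separate ones

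*Protocol article*

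**What the plan says.** Under Mediator analyses, the protocol article hypothesises that the advantage of both active arms over control will be "mediated by reductions in alcohol demand, negative affect (DASS total score) and increases in proportionate substance-free reinforcement". The Present study section names the same three constructs as a secondary hypothesis ("will be mediated by changes in alcohol reinforcing efficacy, negative affective symptoms, and proportionate substance-related reinforcement"). It also predicts that demand, proportionate reinforcement and negative affect will each improve more in the active arms than in control. The section on drinking norms adds a fourth candidate: "Protective behavioral strategies will also be evaluated as a mediator of treatment outcomes".

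The method is fixed: "Mediators will be tested in separate multilevel (mixed) mediation models using the product of coefficients approach". The b-path is described as "the regression of the outcome on the mediator (the “b-path”), with the independent variable included in the model"; no other mediator is named as a covariate. The decision rule is an interval for each product: "The 95% confidence intervals for the mediated effects will be estimated using RMediation".

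An exploratory moderated mediation follows. Demand is expected to carry more of the effect in BAI + SFAS. In RT + SFAS the expectation is that "negative affect (targeted by both the RT + SFAS sessions) will have a larger indirect effect on changes in alcohol use and problems". The article does not say whether mediators are entered together in that analysis.

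**The concern.** With the other mediators left out, the b-path for one construct absorbs the effect of any other mediator that correlates with it within arm. If treatment also moves that construct, the product a × b is non-zero even when the construct itself does nothing to drinking. This happens with perfect time ordering and no effect of drinking on the mediator.

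The article's own hypotheses supply the first condition, a non-zero a-path for three of the four candidates. The second, correlation within arm, is not quantified but is plausible. Under Behavioral economic measures, the demand indices are described as reflecting how strongly alcohol reinforces, and the reinforcement ratio has substance-related reinforcement in its numerator. Both come from the same self-report surveys.

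At stake is what the mediation results can be said to show. The trial asks about several named mechanisms and then contrasts demand in one arm with affect in the other. A significant separate indirect effect does not tell the reader which of these is at work.

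**Working it through.** **The plan's own figures.** The section Sample size and power gives power for drinks/problems of 1.00/1.00 for BAI + SFAS vs control. For mediation it gives 0.90/0.99 (reinforcement), 0.85/0.93 (negative affect) and 1.00/1.00 (demand).

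- A two-sample formula with 175 per arm and d = 0.33/0.32 gives 0.87/0.85 for the treatment effect. Averaging four follow-ups with baseline adjustment (assumed within-person correlation 0.4 to 0.7, baseline correlation 0.5 to 0.7) gives 0.985 to 1.00. The stated 1.00 is therefore plausible.
- The mediation powers cannot be reproduced, because no a- or b-path values are given. If the b-path has power near 1, the a-path implied by 0.90 is (1.96 + 1.28) × √(2/175) = 0.35 SD, and by 0.85 it is (1.96 + 1.04) × √(2/175) = 0.32 SD. An a-path of about 0.3 SD is therefore a reasonable working value.

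**Set-up.** Two arms of 175. M1 is the true mediator, with effect b1 on the outcome. M2 has no effect of its own, but treatment moves it by a2, and it correlates with M1 within arm at ρ. All variables have unit within-arm variance. The values of a2, b1 and ρ are assumptions; the article gives none.

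**Hand check.** In the separate model the coefficient of M2 tends to b1 × ρ, with standard error √((1 − (b1ρ)²)/347). With a2 = 0.33, the a-path z is 0.33/√(2/175) = 3.09, which is significant with probability 0.87. Multiplying the two probabilities approximates the rejection rate:

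- b1 = 0.3, ρ = 0.3: z = 0.09/0.0535 = 1.68, probability 0.39; 0.87 × 0.39 = 0.34.
- b1 = 0.5, ρ = 0.3: z = 0.15/0.0531 = 2.83, probability 0.81; 0.87 × 0.81 = 0.70.

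**Simulation** (4,000 replicates per cell, 95% distribution-of-product criterion, a-path of M1 = 0.33). Rate at which the inert M2 is declared a mediator in the separate model:

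| a2 | b1 | ρ = 0 | 0.1 | 0.2 | 0.3 | 0.5 |
|---|---|---|---|---|---|---|
| 0.33 | 0.3 | 3.6% | 7.0% | 15.7% | 32.8% | 67.1% |
| 0.33 | 0.5 | 3.5% | 11.8% | 37.8% | 68.6% | 86.8% |
| 0.20 | 0.3 | 1.7% | 3.2% | 6.9% | 15.8% | 34.6% |
| 0.20 | 0.5 | 1.3% | 5.8% | 18.0% | 33.1% | 45.0% |
| 0 | 0.3 to 0.5 | 0.2% | 0.4 to 0.5% | 0.5 to 2.2% | 1.5 to 3.8% | 3.3 to 4.9% |

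With M1 and M2 in one model, M2 is declared a mediator in 0.1 to 4.4% of trials. Power for the true mediator is about 0.87 in both models.

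**Closer to the planned data.** Four follow-ups, the article's attrition pattern and negative binomial counts (analysed as log person means with robust standard errors, 2,000 replicates), a2 = 0.33, log-scale b1 of 0.2 to 0.4: the separate model rejects in 13 to 40% at ρ = 0.3 and 32 to 76% at ρ = 0.5. The joint model rejects in 0 to 5.5% over all settings tried.

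**Choice of contrast.** At a = 0.3, b1 = 0.3, ρ = 0.3, repeated runs give about 27 to 29% for one active arm vs control and about 44 to 48% for the pooled active arms (350 vs 175). Both contrasts are planned for the outcome analyses.

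**Causal chain.** Suppose instead that M2 acts through M1: M1 = (a1 − ρ·a2)·T + ρ·M2 + error. This gives exactly the same joint distribution of treatment, mediators and outcome as the set-up above, but M2 now has a genuine indirect effect of a2 × ρ × b1. At 350 vs 175 with a = 0.3, b1 = 0.3, ρ = 0.3, the separate model detects it in about 43% of trials and the joint model in about 3 to 5%.

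**The case against.** The strongest reply is that the two models answer different questions. A separate model estimates a mediator's total indirect effect, including any part that runs through other mediators; a joint model estimates only the part that does not. The chain calculation shows that the same rejection is a false positive under one causal story and correct detection under another, and the data cannot tell them apart. This stands. It rules out making the joint model the sole basis for conclusions, but it does not rescue a plan with no joint model at all.

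Four stronger readings are tempting and are not supported:

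- *The stated null is a unique effect with the other mediators held constant.* The article only hypothesises that each construct mediates. It does not claim exclusive mechanisms, and its power section speaks only of parameters being "rejected for each parameter at alpha = 0.05".
- *All mediators will probably be confirmed when only one is active.* That one-active scenario is an assumption; the article expects all three to be active.
- *The quoted mediation power is partly power to detect correlation with another mediator.* Its inputs come from a previous trial and are not disclosed, so this cannot be verified.
- *The differential hypotheses cannot be answered.* They compare the same mediator's indirect effect between arms, are labelled exploratory, and are not said to hold one mediator each.

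**Conclusion.** The point holds as a cheap improvement. The article commits to one-mediator models with the b-path adjusted for treatment only, and this is a stated choice, not a detail left to a fuller document. Where treatment moves a construct that correlates within arm with a true mediator, the separate test can declare it a mediator well above 5% although it has no effect of its own. For one active arm vs control, with a about 0.3 SD and b of 0.3 to 0.5, the rate is about 5 to 12% at a correlation of 0.1 and about 27 to 69% at 0.3.

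These sizes depend wholly on assumed a, b and correlation values. A smaller a-path lowers them, and a zero a-path or zero within-arm correlation removes the inflation. Correlation that arises only through treatment does no harm, because treatment is in the b-path model. The consequence is limited to the secondary mediation hypothesis and the exploratory differential tests.

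**What to change.** In Mediator analyses, keep the separate models and add, for each outcome, one prespecified parallel multiple-mediator model. Enter demand, negative affect, proportionate substance-free reinforcement and protective behavioral strategies together, with correlated mediator residuals. Use the same structure for the exploratory BAI + SFAS vs RT + SFAS differential tests. Report both sets of results. Describe the separate results as total indirect effects, and claim that a particular mechanism is responsible only where its specific indirect effect is supported in the joint model.

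The cost is some analysis wording and a larger model in Mplus, which is already planned; no new data are needed. There are two downsides. Intervals are wider when mediators are strongly correlated. If the mediators form a causal chain, the specific effect omits the part that passes through the others, so the text should say that a null joint result does not rule out an upstream mediator. The joint model does not address unmeasured confounding of the mediator–outcome relation, or reverse causation where mediator and outcome are measured at the same visit.

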## Sample size and power

We have focused our power analysis using Monte Carlo simulations [64] with population estimates and patterns of missingness from our previous trial [24]. These models from our previous trial used generalized mixed models which covaried gender and race/ethnicity, taking into account clustering by individual and therapist. Based on the Monte Carlo estimates comparing BAI + SFAS to control (within *d* = 0.83/0.71, between *d* = 0.33/0.32), we are proposing to recruit 525 subjects (175 per group) for the study. Assuming a similar pattern of attrition as our previous trial will result in *n* = 362 (69%) complete cases, *n* = 95 (18%) cases missing one data point; *n* = 37 (7%) cases missing two data points; *n* = 21 (4%) cases missing three data points; and *n* = 11 (2%) cases missing four data points. We calculated power via Monte Carlo simulations by determining the proportion of 1000 replications for which the null hypothesis that a parameter was equal to zero was rejected for each parameter at alpha = 0.05 (i.e., probability of rejecting the null hypothesis when it is false). This resulted in the following power estimates for typical drinks/problems: treatment effect of BAI + SFAS vs. control = 1.00/1.00; mediation via proportionate substance-free reinforcement = 0.90/0.99; mediation via negative affect = 0.85/0.93; mediation via alcohol demand: 1.00/1.00. While our proposed sample size would not be sufficient to detect very small effects, we believe such small effects are likely to have little clinical meaning in terms of the variables we are assessing in the present trial, and the necessary sample size to detect such effects would be very large (> 1000).

## Harms

The project director and the principal investigator (PI) will be responsible for overseeing AE and SAE reporting. RAs will take initial reports from participants, and the project director and PI will review for safety and accuracy and recommend follow-up as needed. All AEs and SAEs will be reviewed within five business days. Any SAEs possibly related to study intervention will be reported to the IRB and funding agency within five business days.

## Confidentiality

Data will be collected through participant self-reports completed via computerized assessments and recordings of individual counseling sessions (for treatment fidelity analyses). All data will be collected in secure and private laboratory settings or via a secure, encrypted Zoom call by trained graduate student research assistants/clinicians who have completed university and lab specific training in human subject protections and non-judgmental interviewing techniques. All data are for research purposes and only for the proposed project. The host of the computerized assessment, Rivulent, Inc., contracts with a secure data center that meets industry-standard SAS 70, SSAE 16, and SOC requirements. This ensures physical security protocols including cameras in all sections of the facility, keycard access to server rooms, and locked server cabinets to prevent unauthorized access, even among data center personnel. All data collected is protected in transit by utilizing industry-standard 2048-bit encrypted SSL certificate to ensure data cannot be gleaned through a “man -in-the-middle” style attack. Data is stored within a secure, protected database system, and all personally identifiable information (PII) is stored encrypted using the widely adopted and heavily vetted AES-128-CBC algorithm, which is also the designated encryption method for the United States Government. The server implements industry-standard firewall protection. Following the completion of the assessments, all data will be stored on a secure server stored in the University of Memphis Psychology Department. Our servers are on the university network secured behind our firewall and require user authentication per user to access. The University of Memphis Single Sign-On System (SSO) now includes multi-factor authentication (MFA) capabilities. This means that users can protect their accounts by requiring a second means to authenticate in addition to their password. Participants will be allocated unique trial identification numbers and study data will be associated only with these numbers.

## Data access

Study data will initially be available only to the study Investigators and their labs. After the investigators have published the main outcomes of the trial, they will provide public access to a de-identified data set, consistent with the NIH Policy for Data Management and Sharing.

## Auditing

While the funder does not plan regular audits, the study team is prepared for any possible audits from the funder or the approving IRB.

## Dissemination policy

The research team will disseminate the results of this study through the publication of peer-reviewed manuscripts. All contributing authors will be appropriately credited. In accordance with NIH public access policy, published results will be made publicly available at the NIH National Library of Medicine’s PubMed Central immediately after journal publication. In addition, at the completion of data analysis, all study participants will be e-mailed a copy of a lay summary of the results.

## Discussion

The proposed study has the potential to provide important information on the efficacy of two different brief alcohol intervention approaches with high-risk emerging adults who are not four-year college students or graduates. Notably, there is strong evidence for the efficacy of brief alcohol interventions with college students, but very few studies have explicitly evaluated these approaches with ethnically diverse samples of emerging adults who are not college students (Davis et al., 2017). Moreover, this is the first trial to evaluate two session approaches with this higher risk group, including sessions primarily focused on enhancing substance-free activities and reducing negative affect (RT + SFAS). If effective, RT + SFAS may have greater potential for dissemination than BAI approaches that are generally not used by EAs without sanctions or incentives and that require potentially stigmatizing alcohol screening questions [65, 66]. Should the RT + SFAS successfully reduce alcohol use and negative affective symptoms and increase positive activities it could be disseminated as a brief wellness and goal setting program in a variety of community settings (high schools, vocational training programs, churches, health or community centers) where it could benefit a large population of EAs. Importantly, EAs could benefit from RT + SFAS even if they do not drink or if they do not want to change their use, which should reduce stigma and enhance potential for dissemination.

## Trial status

Recruitment for this trial began on December 8, 2021. We anticipate enrollment to be completed by the end of June 2025. At the time this manuscript is being written, protocol version 4.0 from May 16, 2022, is in use.

### Protocol amendments

All protocol amendments will be submitted to the IRB for approval. The funder will approve all major protocol changes before implementation.

### Reproducible research

At the completion of this study, its protocol will be published on Clinical-Trials.gov, and the corresponding dataset and statistical code will be available upon request to the principal investigator. This manuscript uses SPIRIT reporting guidelines [67]. A SPIRIT checklist is included as an additional file.

## Data Availability

External researchers may submit a request to the investigative team to obtain access to this data for secondary analysis and publication. Data will also be submitted to NIAAA Data Archive (NIAAA_DA_), a data repository housed within the NIMH Data Archive (NDA).

